## Abstract

**Background:**

Heavy cannabis use is associated with adverse physical and mental health effects. Despite available effective treatments, the majority of heavy cannabis users does not seek professional help. Web-based interventions can provide an alternative for cannabis users who are reluctant to seek professional help. Several web-based cannabis interventions are effective in reducing cannabis use; however, the effect sizes are typically small and attrition rates are typically high. This suggests that web-based programs can be an effective cannabis use intervention for some, while others may need additional substance use treatment after completing a web-based intervention. Therefore, it is important that web-based interventions do not solely focus on reducing cannabis use, but also on improving attitudes towards substance use treatment. The Screening Brief Intervention and Referral to Treatment (SBIRT) approach appears to be well suited for the purpose of reducing cannabis use and improving substance use treatment utilization. Based on the SBIRT approach—and based on cognitive behavioral therapy (CBT) and motivational interviewing (MI)—we developed the Internet-based cannabis reduction intervention ICan.

**Methods/design:**

This protocol paper presents the design of a randomized controlled trial (RCT) in which we evaluate the effectiveness of the ICan intervention compared to four online modules of educational information on cannabis in a sample of Dutch frequent cannabis users. The primary outcome measure is frequency of cannabis use. Secondary outcome measures include the quantity of cannabis used (grams), the attitudes towards seeking help and the number of participants who enter specialized treatment services for cannabis use-related problems.

**Discussion:**

To the best of our knowledge, ICan is the first Internet-based intervention for cannabis users that combines screening, a brief intervention—based on CBT and MI—and referral to treatment options.

**Trial registration:**

The study is registered in the Netherlands Trial Register; identifier NL7668. Registered on 17 April 2019.

## Background

Heavy cannabis use in adolescence and young adulthood is associated with various adverse physical and mental health effects [1]. These effects include cognitive impairment and an increased risk of depressive symptoms and suicidal ideation [1]. Heavy cannabis users are at risk for dependence [2, 3]. A longitudinal study of a cohort of (near) daily cannabis users found that almost 40% of the (near) daily cannabis users developed cannabis dependence (DSM-IV) [3].

Treatment programs based on cognitive behavioral therapy (CBT), motivational interviewing (MI), and contingency management are effective in reducing cannabis use [4]. However, the majority of frequent cannabis users does not seek professional help [5, 6]. In the Netherlands, the number of people receiving treatment for cannabis use-related problems increased from 2001 to 2010 and then stabilized until 2015 [7]. In 2015, 11,000 people received treatment for cannabis use-related problems, while according to the most recent estimates (2007–2009) 30,000 people met the criteria for cannabis dependence [7, 8]. Several studies have identified possible explanations for the low numbers of cannabis users entering treatment specifically, and for substance users in general. Commonly reported barriers for seeking treatment are the desire to solve one’s own problems, the feeling that treatment is not necessary, not being ready to stop using cannabis, being unaware of treatments options, not being able to attend treatment during office hours, and stigma associated with substance use disorder treatment [9, 10].

Internet-based programs can overcome some of these barriers and thereby provide an alternative for frequent cannabis users who are unwilling to enter substance use treatment [11]. Internet-based programs are characterized by a high degree of anonymity; this can minimize the fear of being stigmatized [12]. Besides, they are easily accessible, as users can access the programs from any location at any time of day. In addition, the programs can be followed at their own pace, which heightens (perceived) feasibility of following the program. Internet-based programs require less therapist time per patient than face-to-face treatments; therefore, they may also be more cost-effective [13].

Studies show that Internet-based programs for cannabis users are effective. Boumparis et al. recently published a systematic review with meta-analyses on digital prevention and treatment interventions to reduce cannabis use [14]. The meta-analyses showed a small but significant effect in favor of digital interventions compared to control conditions (waiting list, psycho-education or assessment only) [14]. These results are in line with results found in earlier meta-analyses on Internet and computer-based interventions for cannabis use [15–17].

Thus, digital interventions for cannabis users can be effective and have the potential to overcome some commonly reported barriers to treatment-seeking, although effect sizes are generally small. Therefore, they can possibly play an important role in bridging the cannabis use disorder treatment gap. To our knowledge, four Internet-based cannabis reduction programs for the non-clinical population of frequent cannabis users have been evaluated in randomized controlled trials. The first program, a German program called *Quit the shit* is based on the principles of self-regulation and self-control [18]. The 50-day program has a solution-focused approach and includes weekly interaction with a therapist through instant messaging.

The second program, the Australian program *Reduce your Use* consists of 6 modules based on cognitive, behavioral, and motivational principles [19]. The program is fully self-guided; the participants can go through the modules at their own pace.

The third program, the Swiss program *Can Reduce*, is based on CBT, MI, and behavioral self-management [20]. The effectiveness of the program with and without guidance has been tested. The guidance consists of two chat sessions with a trained counselor. The chat sessions have a duration of 20–30 min.

The fourth program, the Swedish program *Cannabishjälpen*, is also based on CBT and MI principles [21]. The program consists of 13 modules. Participants are advised to complete one or two modules per week. At the beginning of the program, a therapist sends a welcome message to the participant including personalized feedback on the baseline assessment. Throughout the program, the participant can contact the therapist if desired.

The Cannabishjälpen program and the unguided version of the Can Reduce program were not effective in reducing cannabis use frequency (compared to the waiting list control condition) [20, 21]. The other programs—*Quit the Shit*, *Reduce your Use* and the guided version of *Can Reduce*—were effective in reducing cannabis use [18–20]. However, the effect sizes were small and attrition was high. These small effect sizes and high attrition rates suggest that online programs can provide an alternative for some, but not for all cannabis users who are reluctant to enter substance use treatment. Therefore, it seems important that online programs do not solely focus on reducing cannabis use, but also on improving attitudes towards substance use treatment. If a cannabis user fails to reduce his use after completing the online program, he may be willing to start/engage in substance use disorder treatment.

The Screening Brief Intervention and Referral to Treatment (SBIRT) approach appears to be well suited for the purpose of improving substance use treatment utilization. The SBIRT approach was developed in the 1960s [22]. The SBIRT approach enables universal screening in a variety of settings, targeting not only those who are already dependent but also those who are not seeking help for their substance use [23]. The screening procedure typically results in three possible outcomes: no risk, moderate risk, or high risk for substance use problems. Substance users at moderate risk for substance use problems receive a brief intervention. The brief intervention usually consists of one or more sessions with a health care professional. The goal of these sessions is to raise awareness about the risks associated with the substance use and to increase motivation to reduce or stop this behavior [23]. Substance users at high risk for cannabis use problems are referred to specialized substance use treatment. The main goal of the referral to treatment is to identify an appropriate treatment program and to facilitate participation of the substance user in the program [23]. The SBIRT approach seems suitable to be computerized.

Based on the SBIRT approach and based on cognitive behavioral therapy and motivational interviewing, we developed the Internet-based cannabis reduction intervention ICan. ICan is an easy to use progressive web app. ICan includes adherence focused guidance to minimize drop-out rates. Users of the ICan app receive weekly WhatsApp messages from a coach to encourage them to use the app. The guidance is minimal to ensure that the intervention remains easily accessible. This protocol paper presents the design of the randomized controlled trial (RCT) in which we evaluate the effectiveness of the ICan intervention.

## Methods

### Aims and hypotheses

The aim of this study is to test the effectiveness of the Internet-based intervention ICan compared to four online modules of educational information on cannabis in a sample of Dutch frequent cannabis users. We address the following research questions: (1) Is the ICan intervention more effective in reducing cannabis use than the control condition? (2) Is the ICan intervention more effective in improving positive attitudes towards seeking professional help for cannabis use-related problems than the control condition?

### Study design

A single blind randomized controlled trial will be carried out with a duration of 6 months in an online setting. The trial will be two armed (ICan intervention x four online modules of educational information on cannabis). Participants will be assessed on cannabis-related outcome measures at T0 (baseline, before randomization), T1 (6 weeks post randomization), T2 (3 months post randomization), and T3 (6 months post randomization). The trial will be conducted and reported according to the most recent version of the Consolidated Standards of Reporting Trials (CONSORT) guidelines [24]. The study is registered in the Netherlands Trial Register; identifier NL7668. Ethical approval to carry out this study was obtained from an accredited medical research and ethics committee in the Netherlands (Medical Research Ethics Committees United, NL67449.100.18). The study is designed and will be performed in compliance with the Declaration of Helsinki, seventh revision.

### Study procedures

Figure 1 shows the CONSORT flow diagram of the trial. Applicants interested to participate fill out an online screening questionnaire to determine if they meet all of the inclusion criteria and none of the exclusion criteria. Applicants who are eligible to participate receive the patient information letter and the informed consent form. Participants have up to 30 days to decide if they want to participate. If they have any questions regarding the study or intervention, they can contact a member of the research team by phone, email, or face-to-face. They can also contact an independent expert whose contact details are listed in the patient information letter. Applicants who decide to participate in the study are asked for necessary personal data. After the participants have sent us their signed informed consent form digitally, they are directed to the baseline questionnaire. The electronic data capture platform Castor will be used for the randomization and allocation procedure and to conduct the online questionnaires. The research data are stored separately from the participants’ personal data. Only the four authors of this study protocol will have access to the keys to join the research data tables with the personal data tables. After the participants have completed the baseline questionnaire, they will be allocated to one of two trial arms (1:1) using variable block randomization. Participants will be informed that they will be assigned to one of two programs, both focusing on cannabis moderation. Depending on the outcome of the allocation procedure, an email will be sent to the participants containing an access code to either the ICan intervention or the online control program (four online modules of educational information on cannabis). Participants will be blind to the condition they are in.

**Fig. 1 Fig1:**
[figure not shown]
Trial flow

The follow-up measurements will take place 6 weeks, 3 months, and 6 months post randomization. Self-reported outcome measures are used to reduce the risk of experimenter bias. If participants do not complete the online follow-up questionnaires, they will first receive an automatic email reminder; subsequently, they will receive WhatsApp (audio) messages to encourage them to fill in the questionnaires. All participants receive the same (audio) messages to reduce the risk of bias.

After completing the 3 months’ follow-up questionnaire and after completing the 6 months’ follow-up questionnaire, the participants will receive a €20 gift card by email. Even if participants discontinue their use of the intervention prematurely, they will be followed up. Only if participants explicitly state that they do not want to participate in the study anymore, data collection will be stopped. After completing the last follow-up questionnaire, the participants are informed about the condition they were allocated to. If desired, they can cross over to the other condition.

All spontaneously reported adverse events will be recorded. All serious adverse events will be reported to the accredited MREC (Medical Research Ethics Committee) that approved the protocol. Given the limited risks associated with a text-based self-help intervention, no Data Safety Monitoring Board or Safety Committee will be established for this study.

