### Intervention condition

The experimental ICan intervention is designed according to the SAMHSA Screening Brief Intervention and Referral to Treatment (SBIRT) framework and is based on cognitive behavioral therapy (CBT) and motivational interviewing (MI). The participant receives an e-mail with an invitation to create an account. The ICan intervention includes adherence-focused guidance. From the moment the participant creates an account, he receives a weekly WhatsApp message from a coach to encourage him to use the app. In the first message(s), the participant is encouraged to complete the self-test and to create the reduce/quit plan. In the subsequent message(s), the participant is encouraged to fill in the consumption diary regularly. Besides the WhatsApp messages, the participant receives motivational push notifications. The participant can set up reminders to fill in the consumption diary. He can indicate how often he would like to receive the reminders and at what time. After 4 weeks, the participant is asked if he is satisfied with the progress he has made so far. If he is not satisfied he is referred to specialized treatment services (see part 4). After these 4 weeks, the WhatsApp messages are discontinued—unless the participant explicitly indicates that he wants to keep receiving the messages. In that case, he receives a weekly message in which he is praised for his achievements in the app—for example completing the additional problem solving exercise, posting a message on the peer support platform, or filling in the consumption diary. The participant keeps receiving these messages as long as he is actively using the app.

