#### Peer support platform

On the peer support platform, participants can write messages to motivate and support each other.

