### Control condition

The control condition consists of four online modules of educational information on cannabis. In the first module, some background information about cannabis is provided. This includes information on the physical and mental effects of cannabis, commonly used consumption methods and cannabis and the law. In the second module, the risks associated with cannabis use are listed. Some tips on how to reduce these risks are given. In the third module, general information about cannabis use disorder is provided. The difference between physical and psychological dependence is explained. The negative social, financial, and health consequences of cannabis use disorder are described, and the DSM-5 criteria for cannabis use disorder are presented. In the last module, some general tips on how to reduce or quit cannabis use are provided. The information used in the four online modules is based on the websites www.drugsinfo.nl and www.drugsenuitgaan.nl. The general tips on how to reduce or quit cannabis use are from an existing information brochure about cannabis use and psychosis [30]. Since the control condition consists of information that is currently available online for non-treatment seeking frequent cannabis users, we considered this to be the standard care (or treatment-as-usual).

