##### Mediators and other measures

The following instruments will be applied to assess their potential role as intervention effect mediator:
l)The number of self-reported cannabis withdrawal symptoms.m)Craving for cannabis will be assessed using the Marijuana Craving Questionnaire Short Form (MCQ-SF) [43].n)The Cannabis Self-Concept Scale (CSCS) will be included to assess identification with cannabis as part of one’s personality or identity [44].o)Self-efficacy to become or stay a non-cannabis smoker will be measured by 6 items used in previous research [45].p)The Marlowe-Crowne Social Desirability Scale (MCSDS) will be included to measure if the respondent has the tendency to give socially desirable responses [46].q)The Brief Symptom Inventory 18 (BSI-18) will be included to assess symptoms of anxiety and depression [47].r)Self-reported substance use (tobacco, alcohol, cocaine, amphetamine, inhalants, sedatives, hallucinogens, opioids, and other drugs).s)Utilization measures will be collected during the use of the intervention: number of logins, number of page views, time spent logged in, and use of major content elements.t)Demographic characteristics of the participant will be collected such as age, sex, and level of education.u)Knowledge obtained about CBT principles will be measured with a self-constructed 5-item questionnaire.v)Knowledge obtained about treatment options/referral to treatment will be measured with a self-constructed 5-item questionnaire.w)The effect of the coronavirus and the coronavirus measures on cannabis use and attempts to reduce/quit cannabis use will be measured with a self-constructed 7-item questionnaire.

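### Spontaneous report is the only stated way of finding adverse events, and contact differs by arm, so recorded counts may be incomplete and not comparable

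*Protocol article*

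**What the plan says.** The safety paragraph of the Study procedures section (after Figure 1) has three elements. On detection: "All spontaneously reported adverse events will be recorded". On serious events: "All serious adverse events will be reported to the accredited MREC (Medical Research Ethics Committee) that approved the protocol". On oversight: "no Data Safety Monitoring Board or Safety Committee will be established for this study", with the low risk of text-based self-help given as the reason. How serious events come to the team's notice is not stated.

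The two programs differ in contact. Under Intervention condition, once an ICan participant has an account, "he receives a weekly WhatsApp message from a coach to encourage him to use the app". The default end is also given: "After these 4 weeks, the WhatsApp messages are discontinued", with continuation on request. The Peer support platform section says that "participants can write messages to motivate and support each other". For the comparator, "The control condition consists of four online modules of educational information on cannabis"; no coach and no peer channel is described.

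Symptom data are collected by questionnaire, but not under a safety heading. In the section Mediators and other measures: "The Brief Symptom Inventory 18 (BSI-18) will be included to assess symptoms of anxiety and depression". Withdrawal symptoms stand in the same list, and health care use (TiC-P) is listed under treatment seeking and cost-effectiveness.

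**The concern.** A spontaneous report depends on two things: that an event happens, and that the participant decides to tell someone. The second depends on how much contact the participant has and with whom. In an online trial without visits, many events may never reach the team. If the arms also differ in how easy it is to mention an event, the counts by arm mix true risk with opportunity to report.

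What is at stake is the harms table. A low count could mean few events or few reports. A difference between arms could mean different risk or different contact. Neither could be read with confidence, even as description and without a formal test.

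**Working it through.** **Step 1: the plan's own figure.** The only design figure is the sample size. A two-sample t-test with d = 0.40, two-sided alpha 0.05 and power 0.80 needs 99.08 per arm, so 100, and power at 100 per arm is 0.804. Allowing for 25% non-response, 200 / 0.75 = 266.7, so 267. Both figures reproduce. Neither uses an adverse-event rate, so this point does not touch them.

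**Step 2: is any other ascertainment method stated?** The secondary, mediator and other measures are listed item by item, ending at (w). The list goes down to 5-item knowledge tests and a 7-item coronavirus questionnaire. No item is described as an adverse-event question, and the legend of Figure 2 names no such instrument. Spontaneous report is therefore the only method that the article states.

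**Step 3: contact by arm.**

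| Route | ICan | Control | Stated link to adverse-event recording |
|---|---|---|---|
| Weekly coach message | Yes, 4 weeks by default, longer on request | Not described | None |
| Peer platform | Yes | Not described | None |
| Research team by phone, email or face-to-face (described at the consent stage) | Yes | Yes | None |
| Reminders to questionnaire non-responders | Yes | Yes, same messages | None |
| Questionnaires at 6 weeks, 3 months and 6 months | Yes | Yes | None |

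The first two rows differ by arm and the last three do not.

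**Step 4: what can be computed.** Let n be the number per arm, p the true risk and s the probability that an event is volunteered, with subscript 1 for ICan and 0 for control.

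- Expected recorded events in an arm = n × p × s.
- Share of events missed in an arm = 1 − s.
- Ratio of recorded events = (p1 / p0) × (s1 / s0). With equal true risk this is s1 / s0.

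If s1 = s0, the ratio is 1: events are missed, but the comparison is not biased. If s1 exceeds s0, ICan shows an excess with no true difference. The article gives none of p1, p0, s1 or s0. Any numerical ratio would only return the values put in, so none is offered.

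**Step 5: can the questionnaires still be changed?** The Study status section dates recruitment from 23 December 2019 to 26 May 2020. On the closing date, anyone randomized before 14 April had passed 6 weeks (42 days), and anyone randomized before 26 February had passed 3 months. Nobody could have reached 6 months before 23 June 2020. For someone randomized on the closing date, the three follow-ups fall on 7 July, 26 August and 26 November 2020. A new item could not have reached every participant at 6 weeks or 3 months. Whether the 6-month questionnaire was still open cannot be told from the article.

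**The case against.** The strongest reply is that light monitoring is a reasoned choice. The intervention is text-based self-help, serious events go to the ethics committee, and no harms hypothesis or claim of safety is made. The article also condenses a fuller protocol: it does not say that events are found solely by spontaneous report, and it may leave the detection of serious events to that document. This stands as a reason for restraint. It does not remove the point, because the article states a method, and that method can be improved cheaply.

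Three stronger readings are tempting, and the document does not support them.

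- A reader might infer that events **will** be captured unequally, to the disadvantage of ICan. Nothing says that the coach or the peer platform receives or forwards adverse events. The coach messages are prompts to use the app, they stop after 4 weeks by default in a 6-month trial, and the peer platform runs between participants. Team contact and reminders are open to both arms.
- A reader might infer that harms would go largely unseen. The BSI-18, withdrawal symptoms, quality of life and health care use are collected by questionnaire and do not depend on volunteering to a coach. They are not designated as harms outcomes, but they could show part of any harm.
- A reader might infer from the exclusion of suicidal ideation, acute psychosis and severe depression that these are the harms the trial expects. An exclusion removes people at higher risk; it does not name safety outcomes.

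The shared routes narrow any difference between arms. They do not cure incompleteness: the team contact still needs the participant to volunteer, and the reminders are described as prompting questionnaires, not as asking about events.

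**Conclusion.** The point holds as a weakness in harms ascertainment. With spontaneous report the only stated method and program contact differing by arm, recorded counts may be incomplete and may not be comparable. Its size is not known: the document allows anything from no arm difference (equal reporting) to a spurious excess in the arm with more contact. The conclusion assumes that the full protocol adds no solicited question; if it does, the point falls away. The primary outcome, its analysis and the sample size are not affected. This is a low-cost improvement, not an error that threatens the trial's main result.

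**What to change.** 1. Add one structured adverse-event question, with the same wording and recall period in both arms, to the questionnaires at 6 weeks, 3 months and 6 months, or to those still to be administered.
2. Report solicited and spontaneous events separately by arm. Give the number who answered the question in each arm as the denominator for solicited events, and the source of each spontaneous report.
3. Tabulate worsening on the BSI-18 by arm as a safety summary, with worsening defined before the arms are compared. This assumes that the BSI-18 is taken at baseline and at follow-up; its timing is in Figure 2, which was not available here.
4. If the questionnaires can no longer be changed, do item 3 and state in the report that spontaneous counts are not comparable between arms.

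The cost is one item in existing online questionnaires and an additional table. The downside is slightly longer questionnaires and more minor events to process. An item added late covers only the remaining follow-ups, and the report should say so.
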